### Standard case management: in hospital

All study patients will be otherwise managed and clinically monitored as per national guidelines; World Health Organization Guideline- Updates on the management of severe acute malnutrition in infants and children (2013). This includes management of dehydration, hypothermia, hypoglycaemia, dermatosis, treatment of infection, eye care, anaemia and vitamin and mineral supplementation. The criteria to transition from F75 to F100 will be as per national guidelines. The discharge criteria from hospital will also be as per national guidelines.

### Co-primary outcome measures

1.Change in MUAC at Day 902.Survival to Day 90

### Secondary outcomes

1.Clinical:a.Weight gain (moderate to good: >5 g/kg/day)b.
*De novo* development of diarrhoea (>3 loose stools/day)c.Time to diarrhoea resolution (if >3 loose stools/day)d.Time to bi-pedal oedema resolution (for those with Kwashiorkor)

2.Changes in intestinal biomarkers:a.Intestinal cell injury (faecal calprotectin)

Supportive biological and physiological data to support end points will include:

A.Anthropometric:a.Weight/height/BMIB.Microbiota:a.Percentage change in relative populations of gut microbiotaC.Metabolomics:a.Changes in generation of short chain fatty acidsb.Changes in host and microbiota metabolic productsD.Lactose intolerance:a.Evidence of stool reducing substances at baseline

### Safety reporting

All relevant adverse events will be reported in the case report form (CRF) and serious adverse event (SAE) forms (
Supplementary File 3). The reporting procedure will be captured within a dedicated safety reporting SOP. At each clinical review the child will be assessed for adverse events, both expected and unexpected. Non-serious and expected events will be routinely captured in the CRF. 

### SAEs

SAEs will be reported immediately to the on-site principal investigator (PI) so that co-PIs may be notified of the event. Serious adverse events include:

1. Any untoward medical occurrence or effect that is: (i) fatal, (ii) life threatening, (iii) permanently or temporarily disabling or incapacitating, (iv) causes prolongation of hospital stay (
*if in the clinician’s judgment the adverse event causes the child to stay in hospital longer than would have been necessary if the adverse event had not occurred*.) or (v) any other event that investigator considers serious, having a real, not hypothetical, risk of one of the previous outcomes.

2. Allergic reactions, which will automatically be considered as SAEs in this pilot study.

A dedicated SAE form will be completed including details of the nature of event, date of onset, severity, corrective therapies given, outcome and causality (i.e. unrelated, unlikely, possible, probably, definitely) (see
Table 2). This data will be reviewed as part of the study monitoring process.

**Table 2. T2:** Assessment of adverse event.

Parameter	Grade 1 mild	Grade 2 moderate	Grade 3 severe	Grade 4 life-threatening/fatal
Estimating severity grade				
Clinical adverse event NOT identified elsewhere in the grading table	Symptoms causing no or minimal disturbance with current illness	Symptoms causing greater than minimal disturbance with current illness	Symptoms requiring corrective medical treatment	Symptoms requiring medical treatment to prevent permanent impairment, persistent disability, or death
Allergic reaction				
**Acute systemic** **allergic reaction**	Local urticaria or flushing with no medical intervention indicated	Allergic reaction: Fever, chills, flushing, limited pruritic rash, nausea and vomiting without generalised angiooedema or bronchospasm	Grade 2 reaction PLUS Generalized urticaria OR angioedema with medical intervention indicated OR Symptomatic mild bronchospasm	Grade 3 reaction PLUS Acute anaphylaxis OR Life- threatening bronchospasm OR laryngeal edema

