### Sample size

Mid-upper arm circumference (MUAC) has been selected as the primary criterion for nutritional recovery because it predicts mortality better and is less affected by oedema than other anthropometric measures, and is also a good index of muscle mass. A recent trial of antimicrobial prophylaxis in Kenyan children admitted with severe malnutrition baseline mean MUAC was 10.6 cm (SD 1.06) and at 90 days, 12.2 cm (SD 1.35), a mean change of 1.6 cm (SD 1.1) nutritional recovery at 90 days
^22^. The overall sample size will be 160 children which will include 80 in each study arm. From the original MIMBLE trial, safety in the study arms were comparable to the standard intervention (manuscript in preparation). As a Phase II study, this study is designed to provide adequate proof of principal that the modified nutritional feed provides clinical, physiological and biological evidence of benefit to the child in terms of nutritional rehabilitation and the predicted effect on biological markers of gut-barrier dysfunction and on the intestinal microbiota. Additionally, it will compare the safety and tolerability of the modified nutritional feed against the current standard of care. The data will thus inform the design and effect size for future pragmatic trials. Formal sample sizes were not calculated; since the study was designed to provide safety data and some indication of the likely efficacy of the modified feed compared to standard of care. We thus aimed to study 160 children in total, which is realistic given the timeframe and funding available for the study. 

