For the control arm, children will receive the standard inpatient hospital management as per national guidelines. Briefly, children will initially receive F75 therapeutic milk at a rate of 130 ml/kg/day, provided at 4-hour intervals. When the child has stabilized (resolved hypoglycaemia, resolved hypothermia and demonstrating appetite) they will be transitioned onto F100 therapeutic milk at the same rate. The rate may be increased by 10 ml per feed, until a maximum rate of 200 ml/kg/day has been achieved. If the child is oedematous, F75 will be commenced at 100 ml/kg/day with 4-hourly feeds until stabilized (the above criteria and the resolution of oedema). When stable the child will transition to F100 formula at the same rate, and if tolerated increase to 130 ml/kg/day. If there is no indication of fluid overload, the feed may be increased by 10 ml per feed to a maximum of 200 ml/kg/day.

For the experimental arm, children will receive pre-packaged modified feeds which are lactose-free and include chickpea (gram) flour as a source of fermentable carbohydrate. The feeds contain: lactose-free skimmed milk powder (7.25%), rapeseed oil (11.5%), gram flour (10%), sugar (9%) and water. All ingredients were sourced from established EU suppliers and passed all required safety tests for human consumption as appropriate for each ingredient (contaminants, pesticides, toxins, bacterial contamination etc.). The final feed contains (per 100 ml): 200 kcal, 18 g total carbohydrate, 5.6 g protein, 12g fat, and 0.4 g resistant starch. The quantity of feed provided will match the total amounts of energy and protein that would be received in the control arm, and additional water provided to match the fluid received.

Treatment with control/experimental treatment will be for 14 days duration, followed by standard treatment outpatient as required. This includes provision of ready to use therapeutic feeds until child has recovered, defined by a weight-for-height z-score >−2. The duration of this is variable.

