**For Intestinal Cell Injury (Faecal Calprotectin)**						
Stool		X	X	X	X	

***Stool assessment.*** Frequency and consistency of stool will be assessed daily until discharge and at day 28 and day 90.

***Dietary recall.*** Children and/or parents/guardians will be asked to complete a 24-hour multi-pass dietary recall via a structured interview to assess the nutritional intake of children on admission, day 28 and day 90 as most children will have progressed onto normal diet with additional RUTF. Intake of standard and modified feeds will be recorded daily during the inpatient episode.

***Day 28 and day 90 follow-up.*** Children will be invited to return to the hospital for a follow-up visit on day 28 and day 90 as a day case which will last approximately 2 hours. This will include a clinical review, anthropometric measurements, and the study investigations outlined above.

***Laboratory investigations.*** Following consent and randomisation, routine admission blood samples will be taken, in accordance to routine clinical practice, for the following investigations: full blood count, clinical chemistry, lactate, glucose, blood culture, malaria status and HIV status. As per WHO guidance all parents will be approached to HIV testing. HIV testing will be conducted with provision of verbal parental or guardian consent. Pre- and post-test counselling will be done in accordance with routine practice. The total admission blood sampling volume equates to 10 ml, the majority of which is for clinical purposes and only includes an extra 3 ml for plasma storage. Routine bloods will also be taken on day 7 and day 28 and day 90 which again will include an extra 3 ml for plasma storage. Plasma will be used for short chain fatty acid and metabolite analysis (
Table 1).

At admission, day 7, day 28 and day 90 stool and urine samples will be taken and be stored. The total volume of urine and stool collected across the study will be 30 ml and 30 g, respectively. Stored samples will be used for metabolite analysis (urine and stool), faecal calprotectin (stool), reducing substances (stool) and DNA extraction for 16S rRNA metataxonomics (stool).

 All stored samples will be sent to Imperial College, London to assess the following:

Intestinal cell injury, by faecal calprotectin assays.Changes in gut microbiota, by 16S rRNA analysis for species related to gut barrier function e.g.
*Bifidobacterium* and

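### The printed SAE definition counts a prolonged hospital stay but does not name a new admission, so whether a readmission after discharge is an SAE depends on another criterion or on the investigator's judgment

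*Protocol article*

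**What the plan says.** The section SAEs opens its list with "Serious adverse events include". It then gives five kinds of event: (i) fatal; (ii) life threatening; (iii) disabling or incapacitating, whether permanent or temporary; (iv) one that "causes prolongation of hospital stay"; and (v) "any other event that investigator considers serious, having a real, not hypothetical, risk of one of the previous outcomes". Allergic reactions are added as automatic SAEs. The explanation attached to (iv) is that the event, in the clinician's judgment, "causes the child to stay in hospital longer than would have been necessary if the adverse event had not occurred".

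On timing, the description of the interventions under Study methods and procedures says: "Treatment with control/experimental treatment will be for 14 days duration, followed by standard treatment outpatient as required". The paragraph on follow-up says: "Children will be invited to return to the hospital for a follow-up visit on day 28 and day 90 as a day case".

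On purpose, the Sample size section says of the study that "it will compare the safety and tolerability of the modified nutritional feed against the current standard of care".

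On handling, an SAE goes at once to the on-site principal investigator and has its own form, which includes causality. Under Safety reporting, adverse events are assessed at every clinical review, and non-serious and expected events go into the CRF. Under Trial monitoring, local monitors look at SAE forms and accumulating data, and there is no Data and Safety Monitoring Committee.

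**The concern.** Item (iv) is the only criterion that refers to hospital care, and its explanation describes a child who is already an inpatient. Read as printed, an event that keeps an inpatient in the ward for one extra day is an SAE. The same event, if it brings a discharged child back to the ward, is not automatically one.

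Most of the 90 days lies after the feeding period, and safety is to be compared between arms. No listed outcome fills the gap. Readmission is neither a co-primary nor a secondary outcome, and Table 1 records length of stay at discharge only. What is at stake is how consistently serious events after discharge are identified, assessed for causality and reported in each arm.

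**Working it through.** There is no figure in the plan to reproduce. The check sets the definition against the follow-up schedule.

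**1. Share of follow-up after the feeding period.** Inputs: 14 days of allocated feed (Study methods and procedures) and follow-up to day 90 (Day 28 and day 90 follow-up).
- Days after feeding: 90 − 14 = 76.
- Share: 76 / 90 = 0.844, or 84%.

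This is time after feeding, not time after discharge. Discharge follows national guidelines and length of stay is not given, so the share of time spent at home may be higher or lower for an individual child.

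**2. Spacing of the scheduled reviews after discharge.** Visits are at days 28 and 90, so the gap is 90 − 28 = 62 days. An admission that begins and ends between those visits is learned of at a scheduled review only if someone asks about it or the family mentions it.

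**3. How each criterion treats a readmission after discharge.**

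| Item | Does it cover a readmission? |
|---|---|
| (i) fatal | Only if the child dies |
| (ii) life threatening | Only if the event is that severe |
| (iii) disabling or incapacitating, including temporarily | Some readmissions, depending on how the term is read |
| (iv) prolonged stay | Not for the event that causes the admission; it can apply again to a later event during that admission |
| (v) investigator's judgment | Possibly; it requires a real risk of an outcome in (i) to (iv), and admission is not among them |
| Allergic reaction | Only if that is the cause |

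No row makes readmission in itself sufficient.

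**4. What follows from the class assigned.**

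| | Classed as SAE | Not classed as SAE |
|---|---|---|
| Record | Dedicated SAE form | CRF |
| Causality assessment | Yes, graded | None described |
| Notification | Immediate, to the principal investigator | None described |

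The class therefore changes how an event is handled, even where the event itself is recorded.

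**5. Number of events affected.** The article gives no readmission rate. An assumed rate multiplied by 160 children would count all readmissions, not those that miss (i) to (iii) and are also judged not serious under (v). The second quantity is the relevant one, and nothing in the article bounds it. No count is offered.

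**The case against.** The case on the other side has four parts.

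- **The list is not closed.** It is introduced as inclusive, (iii) extends to temporary incapacity, and (v) is broad. A severely malnourished child readmitted with sepsis would readily fit (ii), (iii) or (v). This stands. A reader might infer that readmissions are excluded from the SAEs, and the text does not support that.
- **The event need not be lost.** Adverse events are assessed at each clinical review, and the day-28 and day-90 visits include one. Deaths are counted through the co-primary survival outcome whatever the SAE wording. Monitors also see accumulating data, not SAE forms alone. This stands too. A reader might infer that the safety comparison undercounts harm. What the article supports is narrower: SAE classification may be inconsistent.
- **Unseen documents may settle it.** The safety SOP and the SAE form (Supplementary File 3) are not shown and could name admission. That is possible. However, Safety reporting assigns the reporting procedure to the SOP, not the definition. If either document does name admission, it goes beyond the list printed here and the two should be aligned.
- **No endpoint is biased, and admission is itself a clinical decision.** No SAE rate is a listed outcome, and an admission criterion would not remove open-label judgment. Both are correct. An admission is, however, a dated fact that can be counted in the same way in both arms. The judgment in (v) is a second discretionary step placed on top of it.

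**Conclusion.** The point holds in a limited form. As printed, the definition treats the same event differently according to whether the child is still in hospital. After discharge, a readmission that is not fatal, life threatening, or disabling or incapacitating becomes an SAE only by investigator judgment. This is a weakness in a stated rule, not a detail that an article would leave to another document. It matters here because safety comparison is an aim, 84% of the 90 days follows the feeding period, allocation is known to those who classify events, and there is no Data and Safety Monitoring Committee.

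The effect cannot be sized. The article gives no readmission rate, and it gives no basis for saying which arm would have more or fewer events classed as serious. A claim that either arm is favoured, or that a particular number of SAEs will be missed, would go beyond the document. The conclusion assumes that the printed list is the operative definition; the SAE form and SOP should be checked on this.

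**What to change.** - Reword item (iv) to: *requires new hospital admission or prolongs an existing hospital stay*. Bring the SAE form and the safety SOP into line with it.
- At the day-28 and day-90 visits, ask about any hospital admission since discharge, and record its date and reason.
- Report readmissions by arm to day 90, whether or not each was classed as an SAE.

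The cost is one line in the protocol and the form, one question at two visits that are already scheduled, and a few more SAE reports. Enrolment began in July 2018, so the change would go through the amendment route described under Protocol version changes. Children already enrolled can be asked at their remaining visits. The report should say from what date the revised definition applied. Both arms would change on the same date.

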### Trial monitoring

This Phase II will be monitored locally, by designated GCP trained and experienced monitors, through assessment of any SAE forms and accumulation of data collected. There is no Data and Safety Monitoring Committee and no planned interim analyses.

### Data management and statistical analysis

Information will be stored securely and will only be made available to those caring for the child and those directly involved in the study. Any reports will not mention the names of the child or parent/guardian. Patient admission data collection forms and observation charts will be kept in a locked cupboard. Designated members of the research team will transcribe relevant data from the source documents to the CRF. Data entry will be done through
OpenClinica, an FDA-approved, web-based application, to a relational PostgreSQL database. Security is enforced through authentication of users by use of encrypted passwords. Different access level accounts authorize users on actions they may perform on the database.

Data will be analysed on an intention-to-treat basis. Differences in outcome measures between the three treatment groups will be compared with ANOVA or linear regression as appropriate. Where variables are not normally distributed, they will be transformed by taking logarithms. If this is insufficient, then equivalent non-parametric tests will be used. Metabolomic data will be analysed using multivariate statistical techniques including principal components analysis, projection to latent structures (PLS) and orthogonal PLS.

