### Study methods and procedures

***Screening procedure.*** Dedicated trial research nurses will be employed to conduct the study. Eligible children will be identified by the nurse and clinician on duty and registered in the eligibility screening log. A member of the trial team will then perform a structured clinical assessment of WHO anthropometric and clinical criteria to confirm severe acute malnutrition and any exclusion criteria.

Details of those fulfilling the entry criteria will be entered onto a screening form, while reasons for non-eligibility will be added to the eligibility screening log. It is anticipated that this process will take approximately 10 minutes.

***Consent.*** Prospective written, informed consent will be sought from parents or guardians of children. Parents or guardians will be given an information sheet in their usual language containing details of this pilot study. The sheet will be read aloud to those who are unable to read. Parents and guardians will be encouraged to ask questions about the trial prior to signing the consent form (
Supplementary File 1). For parents who are unable to sign the consent form, a thumbprint will be required and a witness will be required to sign the consent form.
Supplementary File 2 contains the information given to the parents/guardians of each child in the study.

***Randomisation.*** Randomisation is in permuted blocks. The sequence was generated by a data manager at KEMRI Wellcome Trust Research Programme (KWTRP), Kilifi, Kenya. This sequence was used, by a study administrator, to prepare cards with treatment allocation (standard or altered standard with chickpea flour) at the Clinical Trial Facility, KWTRP, Kilifi, Kenya. The randomisation cards were sent to MRCI, Mbale. The cards will be kept in numbered, sealed opaque envelopes, each signed across the seal. The randomisation cards are numbered consecutively and the dedicated MIMBLE clinical trial team will select the next card in the sequence ie cards will be opened in numerical order when enrolling a patient in the clinical trial.

***Study interventions.*** Children will be randomly allocated on a 1:1 basis to:

Control arm: World Health Organization recommended F75 (0.75 kcal/ml) and F100 (1 kcal/ml) feedsExperimental arm: Lactose-free, chickpea enriched feed containing 2 kcal/ml, provided in quantities to match energy provision in standard treatment.

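### The analysis section compares three groups in a two-arm trial, and its single rule for continuous outcomes does not fit the resolution times or, at its log step, the 0/1 outcomes

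*Protocol article*

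**What the plan says.** The protocol article gives its comparative method in one place, the section Data management and statistical analysis. After declaring intention to treat, it says: "Differences in outcome measures between the three treatment groups will be compared with ANOVA or linear regression as appropriate". Two fallbacks follow: "Where variables are not normally distributed, they will be transformed by taking logarithms", and then "If this is insufficient, then equivalent non-parametric tests will be used". The only other methods named are multivariate techniques for the metabolomic data.

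Everywhere else the trial has two arms. Under Study methods and procedures, "Children will be randomly allocated on a 1:1 basis to" is followed by one control arm and one experimental arm. Sample size says "The overall sample size will be 160 children which will include 80 in each study arm". The abstract and Study design agree.

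The outcomes are of mixed type. The co-primary outcomes are change in MUAC and "Survival to Day 90". The clinical secondary outcomes are weight gain (written with a threshold of more than 5 g/kg/day), de novo diarrhoea, "Time to diarrhoea resolution (if >3 loose stools/day") and time to oedema resolution. On measurement, the Stool assessment paragraph says: "Frequency and consistency of stool will be assessed daily until discharge and at day 28 and day 90".

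**The concern.** There are two faults in one sentence. The number of groups contradicts the design, so the sentence does not describe the contrast that the trial randomises. And one rule is set for outcome measures as a whole, although its steps assume a continuous outcome observed in every child.

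The second fault matters most for the two resolution times. A child who dies with diarrhoea or oedema has no resolution time. A child discharged unresolved is next assessed at day 28, so the time is known only to lie in an interval. ANOVA, linear regression and ordinary rank tests need a value for each child, and the protocol does not say what value these children get. If they were left out, the comparison would be restricted to children selected by something that happens after randomisation and that the feed may affect. That would sit badly with the declared intention-to-treat analysis.

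For survival and de novo diarrhoea the difficulty is narrower: the log step has no meaning for a 0/1 variable, and simple regression on survival takes no account of children lost before day 90.

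**Working it through.** **Number of groups.** Two arms of 80 give 2 × 80 = 160, the stated total. Three equal groups would need 160 / 3 = 53.3 children each. No third group is described anywhere in the article.

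**Outcome types** (two co-primary and four clinical secondary outcomes):

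| Outcome | Type | Does the stated rule fit? |
|---|---|---|
| Change in MUAC | continuous | yes |
| Survival to day 90 | 0/1 or time-to-event | regression only with complete vital status; log step no |
| Weight gain | 0/1 by threshold, or continuous in g/kg/day | only if continuous |
| De novo diarrhoea | 0/1 | log step no |
| Time to diarrhoea resolution | time-to-event | no |
| Time to oedema resolution | time-to-event | no |

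Four of six do not fit the full rule, or five if weight gain is analysed by its threshold. Faecal calprotectin and the supportive continuous measures do fit.

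**The fallbacks on a 0/1 outcome.** Such a variable is never normally distributed, so read literally the rule sends it to logarithms. Log(0) is undefined, and any transformation of a two-valued variable leaves it two-valued.

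**Linear regression on survival.** Simulated type I error with 80 per arm, complete follow-up and a two-sided 0.05 level (the level is an assumption; the article states none), 20,000 trials per row:

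| Mortality in both arms | Type I error |
|---|---|
| 5% | 4.0% |
| 10% | 4.9% |
| 20% | 4.9% |

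This is close to nominal, and the coefficient is a risk difference.

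**How many children the resolution question touches.** The Introduction cites diarrhoea in 65% of such children, with 20% mortality. If both figures applied here, 0.65 × 160 = 104 children would have diarrhoea and 0.20 × 104 = 20.8, about 21, would die. How many would die before resolution is not given.

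**What omission could do (hypothetical).** Suppose 80% of controls resolve at a mean of 4 days and 20% die unresolved. Suppose the experimental arm has the same 80% at 4 days plus a further 10% who survive and resolve at 8 days. Means among resolvers:

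- control: (0.8 × 4) / 0.8 = 4.0 days
- experimental: (0.8 × 4 + 0.1 × 8) / 0.9 = 4.44 days

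The arm in which more children resolve (90% against 80%) looks 11% slower, since 4.44 / 4.0 = 1.11. Only the 20% mortality comes from the article; the rest is assumed.

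**Type I error on logged resolution times.** Assumed inputs: 50 affected children per arm, exponential resolution with mean 5 days in both arms, independent exponential censoring, no separate modelling of death, 3,000 trials per row.

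| Mean censoring time, arm A vs arm B | t-test, unresolved left out | t-test, unresolved set to last observation | Log-rank |
|---|---|---|---|
| 10 vs 10 days | 5.3% | 5.4% | 6.0% |
| 15 vs 7 days | 11.6% | 15.8% | 4.8% |
| 20 vs 5 days | 32.2% | 45.6% | 5.3% |

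With equal censoring there is no inflation. With unequal censoring there is, and its size follows entirely from the assumed gap.

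**The case against.** The word for three looks like a drafting slip. Every other section gives two arms, so nobody would run a three-group comparison. A reader might infer that a third arm was planned or dropped. Nothing supports that: Protocol version changes mentions legume sourcing and a recruitment site, not an arm. The slip is still a contradiction and needs correcting.

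A journal article may leave outcome-by-outcome methods to an analysis plan, and the rule can be read as a generic one for quantitative variables. This stands in part. The absence of a censoring rule or a named survival model would be no finding by itself. But the article does not defer. It sets a rule for outcome measures without limiting it to continuous ones, and on its plain reading the phrase allowing choice selects only between ANOVA and linear regression.

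A reader might go further and infer that co-primary survival cannot be validly analysed as written. That is too strong. With complete day-90 vital status, linear regression gives a risk difference at near-nominal error, and a rank test on 0/1 data is in effect a comparison of two proportions. The weakness appears with loss before day 90, for which no rate is given.

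A reader might also infer that unresolved children will be dropped and the result reversed. No section says they will be excluded. Intention to treat is declared, and a rank test could give them the worst rank. The 4.0 against 4.44 days and the 12% to 46% error rates show what could happen under assumed inputs, not what this trial will show.

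Finally, this is a pilot phase II trial without a formal sample size. That limits the consequences but does not make the stated rule fit.

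**Conclusion.** The point holds in limited form. The group count is wrong on the face of the document. The single rule does not suit the two resolution times, and its log step is undefined for survival and de novo diarrhoea; together these are four of the six clinical outcomes, or five with weight gain taken by its threshold. Because a method is stated and fits badly, this is more than detail left to an analysis plan.

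No numerical size can be fixed for the harm. For survival it is small if day-90 vital status is complete. For the resolution times it ranges from none, when censoring is equal between arms, to substantial, when it is unequal and unresolved children are left out or given their last observed time. The article gives neither the death and discharge patterns nor the handling that would place this trial in that range.

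**What to change.** Replace the reference to three groups with the two randomised groups, and state a method by outcome type:

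- **Survival to day 90:** Kaplan-Meier with log-rank or Cox, and the day-90 risk difference with 95% CI.
- **Binary outcomes** (de novo diarrhoea, and weight gain if the threshold is kept): risk difference and risk ratio with 95% CI.
- **Times to diarrhoea and oedema resolution:** time-to-event methods with death as a competing event. For children discharged unresolved, use the day 28 and day 90 assessments through interval censoring rather than censoring everyone at discharge; otherwise censor at the last assessment. For oedema this assumes that it is recorded in the clinical review at those visits.
- **MUAC, calprotectin and the other continuous outcomes:** keep linear regression, with log transformation where needed.

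The cost is wording in the protocol or analysis plan, ideally settled before outcome data are compared by arm. No new data, visits or patients are needed, and the sample size does not change.
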